## **ABBREVIATIONS**

AE Adverse event

AR Adverse reaction

APACHE Acute physiology and chronic health evaluation

CRF Case report form

DIC Disseminated intravascular coagulation

eCRF Electronic case report form

GCP Good clinical practice

HREC Human research ethics committee

ICU Intensive care unit

MODS Multiple organ dysfunction syndrome

RCT Randomized controlled trial

SAE Serious adverse event

SAR Serious adverse reaction

SOD Superoxide dismutase

SOFA Sequential organ failure assessment

# **Efficacy of Xuebijing Injection in Patients with Sepsis: A Multicentre, Randomized, Blind, Placebo-controlled Trial**

## **EXIT-SEP PROTOCOL**

### **1. INTRODUCTION**

Despite significant advances over the past several decades, mortality from sepsis remains unacceptably high. A study suggested global estimates of 31.5 million sepsis and 19.4 million severe sepsis cases, with potentially 5.3 million deaths annually [1]. A retrospective cohort study of adult patients revealed sepsis in 6% of adult hospitalizations, of which 15.0% died in the hospital [2]. Even though the mortality of septic shock has declined over the past 10 years along with the advancement of the medical industry, the overall mortality of septic shock still reaches up to 40% [3].

The introduction of new Sepsis-3 criteria [4] has facilitated clinician differentiation of sepsis from common infections and prescription of effective treatment and management in a timely manner. However, the available therapeutic strategy for sepsis is limited to antibiotic administration and supportive care, since current therapeutic measures targeting septic pathological processes (such as inflammatory response, blood coagulation and immunologic dysfunction) are less promising. Therefore, exploring effective therapeutic medications for decreasing the severity and improving the prognosis of sepsis is of significant scientific and social value.

Sepsis is involved in a complex neuroimmune-endocrine response to pathogens instead of pathogen-induced direct damage to local tissues. In addition to inflammatory and anti-inflammatory responses, infection can also lead to abnormalities in endocrine function, metabolism, blood coagulation, and eventually organ dysfunction. Among all pathological changes, the inflammatory response and immune dysfunction play a critical role in the development of sepsis [5]. The state of immunoactivation is not sustained during the process of sepsis. Indeed, a study has shown that the initial hyperinflammatory response in

sepsis (manifested by excessive secretion of inflammatory mediators) is quickly followed by the development of a sustained anti-inflammatory or immunosuppressive state. Moreover, such proinflammatory and immunosuppressive responses might also coexist in the early stage of sepsis.

In the initial stage, infection activates phagocytic cells and facilitates their enhanced phagocytic and killing functions. These activated phagocytic cells secrete excessive cytokines (e.g., IL-1, IL-6, IL-8, IL-12, and TNF- $\alpha$ ), which subsequently induce an inflammatory response and blood vessel dilatation and eventually increase blood vessel permeability. Moreover, activated macrophages can act as professional antigens and induce specific immune responses. Along with disease progression, the proliferative ability of lymphocytes gradually declines, which manifests as immune responses dominated by T helper lymphocytes (Th2) and excessive lymphocyte apoptosis. When massive apoptosis of immune cells (including T cells, B cells, macrophages, and dendritic cells) is induced by excessive inflammatory factors[6], immune effector cells can only secrete fewer cytokines, become hyporesponsive and present impaired antigen presenting capability. As a consequence of these immunosuppressive processes, the body loses “immunological surveillance”, becomes less sensitive to pathogens with immune dysfunction, and eventually develops multiple organ dysfunction syndrome (MODS) or even death.

Previously, immunotherapy against inflammatory mediators has failed to improve survival in patients with sepsis. Different types of anti-inflammatory medications, such as interleukin-1 receptor antagonist, anti-bradykinin, anti-TNF antibody, soluble TNF receptor, platelet activating factor receptor antagonist, platelet activating factor, acetylhydrolase and anti-prostaglandin, were tested in preclinical and clinical trials. However, none of these agents could significantly improve patient survival in clinical trials, even with acceptable results in preclinical trials[7]. It seems that simple anti-inflammatory mediators cannot reverse the pathophysiological changes related to sepsis since patients also have immune dysfunction.

The status of immune function determines the prognosis of patients with sepsis. With the constant in-depth exploration of septic pathogenesis, immunoregulation therapies have

gained increasing attention. Recent clinical studies have shown that the regulation of immune function may improve the prognosis of patients with sepsis.

The immune function status of sepsis might vary among patients with different basal states or under different disease courses. Immune enhancement, the apparent inflammatory response and tissue damage are predominant in the early stage of sepsis[8]. Moreover, when HLA-DR expression and inflammatory factor production by monocytes cannot recover for sepsis patients in a severe stage, immune paralysis status significantly worsens the prognosis [9]. A study showed that an immunoregulator, thymosin alpha 1 (Zadaxin), can improve clinical outcomes for patients with elderly severe sepsis [10]. Comparatively, for young sepsis patients, the anti-inflammatory agent ulinastatin might also improve the prognosis and shorten hospitalization duration and ICU stay [11].

Therefore, either an excessive inflammatory response or unbalanced immune function prevails, and abnormal host responses to infection are considered the most fundamental cause of organ failure in patients with sepsis. Hence, regulation of the host response in patients is currently an important target for exploring new drugs and therapies. Xuebijing injection could serve as an effective therapeutic agent for sepsis due to its effects of inhibiting inflammation, improving immunity and regulating the coagulation balance.

Xuebijing injection was prepared with Carthami Flos (Hong Hua, 红花), Paeoniae Radix Rubra (Chi Shao, 赤芍), Chuanxiong Rhizoma (Chuan Xiong, 川芎), Salviae Miltiorrhizae Radix Et Rhizoma (Dan Shen, 丹参) and Angelicae Sinensis Radix (Dang Gui, 当归). Pharmacological studies have demonstrated that Xuebijing injection might inhibit endotoxin, control the uncontrolled release of endogenous inflammatory mediators produced by endotoxin-induced monocytes/macrophages, improve the coagulation function in disseminated intravascular coagulation (DIC), increase superoxide dismutase activity, regulate both hyper and hypoinmunoresponses, and protect and repair damaged organs under stress. In summary, Xuebijing injection can antagonize endotoxin; inhibit inflammatory mediators; improve immune function; restore coagulation balance; and protect tissues and organs.

A study has shown that Xuebijing injection protects major animal organs after severe injury mainly by inhibiting the synthesis and release of high mobility group box 1 (HMGB-1), a late-acting inflammatory mediator, and subsequently preventing the occurrence and progression of sepsis and MODS or improving the prognosis[12].

Xuebijing can effectively release the proliferation-inhibitory status of septic effector T cells (Teff) by inducing the apoptosis of regulatory T cells (Treg) through the Caspase3/9 pathway and then significantly regulating the immune disorder caused by sepsis. It can also promote the proliferative activity of T cells through CD11clowCD45RBhighDC, improve cellular immune function, and ultimately reduce mortality. In addition, Xuebijing can promote M2 polarization of macrophages, improve the inflammatory response and prognosis, and reduce mouse mortality[13].

Xuebijing injection can also improve coagulation and endothelial function. Animal experiments have demonstrated that Xuebijing injection significantly reduces the levels of plasma IL-6 and TNF- $\alpha$  in rats with sepsis by reducing the tissue factors (TFs) of monocytes and downregulating protease-activated receptors (PAR-1), improves coagulation function, and recovers platelet function [14]. In an experiment using qualitative detection with Tachypiens amebocyte lysate (TAL), Xuebijing injection exhibited a direct inactivation effect on endotoxin in vitro. More specifically, the minimum antitoxic concentrations for the 1-hour and 4-hour reactions were 0.125 mg/ml and 0.063 mg/ml, respectively. Xuebijing injection reduces endotoxin-induced lethality in mice.

In DIC model rats, it improves coagulation function and increases the levels of platelets and fibrinogen. It also shortens the thrombin time (TT) and prothrombin time (PT) and increases the platelet aggregation rate. Moreover, it reduces plasma thromboxane B2 (TX B2) levels. Additionally, it has a therapeutic effect on endotoxin-induced toxic injury of the rat liver and can increase superoxide dismutase (SOD) activity. Furthermore, it has an antagonistic effect on the increase in tumour necrosis factor- $\alpha$  (TNF- $\alpha$ ) serum levels in endotoxin-stimulated mice, and it can increase serum anti-goat red blood cell antibody levels to improve humoral immune function in sensitized mice accordingly. Additionally, it increases the clearance index K, the phagocytic index  $\alpha$ , and the phagocytic activity of the reticuloendothelial system in normal mice [15].

Clinical studies have also shown that Xuebijing injection inhibits the activation of the inflammatory response during sepsis, reduces the occurrence of coagulation dysfunction, alleviates the development of sepsis and improves the prognosis of patients with sepsis [16]. A systematic review of Xuebijing injection for the treatment of sepsis recruited 25 articles, including 1970 cases (1022 cases in the Xuebijing group and 948 cases in the control group), and considered 28-day mortality as the main evaluation indicator. The results showed that the 28-day mortality for patients receiving both Xuebijing injection and conventional treatment [relative risk (RR)=0.65, 95% CI 0.54 - 0.79] was lower than that for patients receiving only conventional treatment, and the improvement in APACHE II scores after 7 days and 14 days of treatment was better than that in the conventional treatment group (WMD = 3.74, 95% CI 2.05 - 5.43; WMD = 10.50, 95% CI 1.43 - 19.57, respectively). Therefore, this systematic review demonstrated that Xuebijing injection could reduce the 28-day mortality of patients with sepsis and improve the APACHE II score [17]. Another randomized controlled trial also showed that Xuebijing injection could markedly reduce the severity of patients with sepsis, promote organ function recovery, regulate coagulation dysfunction and improve the prognosis in a safe manner [18].

Anti-sepsis medication still relies on antibiotics, and no medicine can be provided for definite improvement of the mortality of sepsis patients. Xuebijing injection may improve the prognosis of sepsis patients by regulating immune inflammation and coagulation. Sepsis-3 diagnostic criteria focus more on the impact of organ dysfunction on the prognosis of patients, while Xuebijing injection may increase the survival rate of patients with sepsis by improving organ function. Therefore, it is necessary to conduct a multicentre, blind, randomized and controlled clinical study to evaluate the effect of Xuebijing injection for sepsis patients with 28-day all-cause mortality as the primary endpoint.

## **2. TRIAL OBJECTIVES**

To evaluate whether Xuebijing Injection, when administered to subjects with sepsis, can reduce 28-day all-cause mortality.

### **3. OVERALL STUDY DESIGN**

#### **3.1 Study design**

This is a prospective, multi-centre, randomized, blind, placebo controlled trial.

#### **3.2 Study population**

Patients admitted to any ICU of the participating hospitals with the primary diagnosis of sepsis 3.0 will be screened for inclusion into this study.

#### **3.3 Inclusion criteria**

- 1) Subjects is diagnosed with sepsis 3.0
- 2) A ge  $\geq 18$  years and  $\leq 75$  years
- 3) Subjects had a Sequential Organ Failure Assessment (SOFA) score of 2-13
- 4) Subjects must be receiving treatment in an intensive care unit (ICU)
- 5) Informed consent obtained from patient or legally authorized representatives

#### **3.4 Exclusion criteria**

- 1) Subjects is diagnosed with sepsis for more than 48 hours
- 2) Female who is pregnant or lactating at time of admission
- 3) Had severe primary disease, including unresectable tumors, hematological diseases and human immunodeficiency virus (HIV) infection, had severe liver and kidney dysfunction (was defined as a liver or a kidney component SOFA score  $\geq 3$  points)
- 4) Receiving/took an immunosuppressant, an organ transplant within the previous 6 months
- 5) Participated in other clinical trials in the previous 30 days

### **4. STUDY PROCEDURES**

#### **4.1 Summary of study treatment**

All eligible ICU patients will be enrolled as soon as possible after fulfilling the criteria for randomization. Patients will be allocated in a 1:1 ratio to either the treatment group, receiving Xuebijing Injection, or to control group, receiving placebo.

## 4.2 Study drug

### 1) Xuebijing Injection

Tianjin Chase Sun Pharmaceutical Co., Ltd. (National Medicine Permit No. Z20040033)

Xuebijing injection is prepared by Carthami Flos (*Hong Hua*, 红花), Paeoniae Radix Rubra (*Chi Shao*, 赤芍), Chuanxiong Rhizoma (*Chuan Xiong*, 川芎), Salviae Miltiorrhizae Radix Et Rhizoma (*Dan Shen*, 丹参) and Angelicae Sinensis Radix (*Dang Gui*, 当归). Glucose and polysorbate 80 are also added as excipients (for injection).

This product is a clear pale brown liquid.

[Specification] Ten millilitres of Xuebijing injection per ampoule; 5 ampoules per pack.

[Storage] Sealed and stored in a cool ( $\leq 20^{\circ}\text{C}$ ), dry place away from light.

[Package] Xuebijing injection is packed with a low borosilicate glass ampoule. The secondary package is the “Xuebijing injection package for scientific purposes”.

### 2) Placebo

0.9% sodium chloride injection, consisting of 250 ml in-service products packaged in subsites; HANACO® lightproof infusion set and light shield, provided by the manufacturer for free.

## 4.3 Randomization

This study adopts a third-party interactive web response system (IWRS), which is implemented as competitive enrolment with a randomized block design. The random process is blinded to the investigators. Subjects are assigned to the treatment group and the placebo group at a 1:1 ratio.

When the screened subjects are eligible for recruitment, investigators at subsites log in to the IWRS and enter the subjects' basic information, including their screening numbers and initials, according to the system prompts. The IWRS randomly assigns the subjects SOFA scores (2-7 points vs. 8-13 points) as a stratification factor. The SSID (6 digits) and random number (4 digits) of each subject are unique and bound to each other.

After random numbers are generated, drug managers log in to the IWRS again for the allocation results and then provide this information to study nurses and dispense the investigational products to study nurses for instillation.

#### 4.4 Blinding

Investigators and drug managers have independent access to the IWRS for login and operation. The blinded code is concealed by the IWRS to prevent investigators from obtaining it. The case report form (CRF) only indicates the random number of a subject without group information. Investigators and evaluators do not know the subject group information during the study and evaluation. The investigational drugs are infused with opaque brown bags and tubing to prevent investigators and other participants in the study from knowing the group information.

[figure not shown]

**Figure 1. Blinding of the drug used in the Xuebijing group and placebo group**

The trial drug covered by opaque brown bags and tubing (Figure 1). During the study, only drug managers and study nurses who prepared the study drugs are aware of the allocation information of subjects, but they do not participate in the data collection and outcome evaluation of the study. All study participants should sign a letter of confidentiality commitment to avoid disclosing blinded treatment information.

#### 4.5 Duration of Study Treatment

Treatment will continue until one of the following criteria for treatment cessation is met:

- 1) For Xuebijing group-5 days of Xuebijing Injection treatment has been administered
- 2) For control group -5 days of placebo has been administered

- 3) Patient is discharged from ICU
- 4) Death occurs
- 5) Serious adverse events suspected to be related to a study medication develops
- 6) Development of a contraindication to any of the study drugs
- 7) Consent has been withdrawn or consent to continue has not been granted

#### 4.6 Concomitant Treatment

All patients enrolled in this study will be managed by a standardized approach which will include the following elements:

International Guidelines for Management of Sepsis and Septic Shock: 2016, including early fluid resuscitation, anti-infection, hormone usage, anticoagulation therapy, intravenous nutrition, and other therapeutic methods. The use of anti-infective agents, hormones, and anticoagulants should be recorded in detail: the generic names, dosage, number of doses per day, and duration.

Anti-infective agents: Antiviral agents and antifungal medications can be prescribed in accordance with the methods recommended by relevant guidelines and expert consensus; antibacterial agents should be prescribed in accordance with the recommended methods of Surviving Sepsis Campaign: International Guidelines for Management of Sepsis and Septic Shock: 2016;

Circulation support: Blood pressure should be maintained above 90 mmHg/60 mmHg, and mean arterial pressure should be  $\geq 65$  mmHg; Vasopressors could be prescribed depending on the conditions of the disease, including dopamine, dobutamine, epinephrine, norepinephrine, etc., and norepinephrine should be prioritized. The dose of vasopressors should be recorded at any time upon usage.

Nutritional support: Enteral nutrition should be prioritized for patients with mechanical ventilation, and intravenous nutrition can be prescribed when the following indications occur: Patients cannot ingest food through the gastrointestinal tract due to oesophageal fistula, intestinal fistula, gastrointestinal malformation, or other conditions; Serious trauma or inflammation of the gastrointestinal tract; Serious gastrointestinal dysfunction, such as ulcerative colitis, gastrointestinal haemorrhage, and other conditions;

Ingestion through the gastrointestinal tract is dangerous, such as tracheoesophageal fistula, laryngeal insufficiency, and other conditions. These patients should receive deep intravenous feeding.

The ICU team will have full and independent control of patient management, which will not be affected by participation in the study.

#### 4.7 Interventions prohibited during the trial

- 1) During the treatment period, ulinastatin are prohibited.
- 2) Ulinastatin and Xuebijing injection are prohibited from the end of the treatment period to the 28-day follow-up.

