| Treatments                   | 
Treatment group: Xuebijing injection (100 ml, every 12 hours) diluted in 100 ml 0.9% sodium chloride injection
 
Placebo group: 0.9% sodium chloride injection (200 ml, every 12 hours)
                                                                                                                                                                                                                                                                                                                                                                                                                                                                                                                                                                                                                                                                                                                                                                                                                                                                                                        |
| Duration of Treatment        | Active treatment will continue for 5 days, discharge from study hospital, discharge from the ICU, study withdrawal, or death, whichever comes first.                                                                                                                                                                                                                                                                                                                                                                                                                                                                                                                                                                                                                                                                                                                                                                                                                                                                                                                                                              |

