### 7.4 Protocol Deviations

A protocol deviation is an unanticipated or unintentional departure from the expected conduct of an approved study that is not consistent with the current research protocol or consent document. A protocol deviation may be an omission, addition or change in any procedure described in the protocol. Given that the investigator is responsible for patient

safety and care he/she may implement a deviation from, or a change of the protocol to eliminate an immediate hazard to trial patients without prior Human Research Ethics Committee approval. The implemented deviation or change must be reported in a protocol deviation form. The deviation must be reported via the study website by the principal investigator. A summary of protocol deviations will be reported to the coordinating Human Research Ethics Committee; a serious breach will be reported ASAP.

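### The prohibited-interventions list bars non-study Xuebijing only after the treatment period, leaving it without an express bar in the days that create the randomised contrast

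*Protocol*

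**What the plan says.** Protocol section 4.7 has two items. The first covers the treatment period: "During the treatment period, ulinastatin are prohibited". The second covers the time after it: "Ulinastatin and Xuebijing injection are prohibited from the end of the treatment period to the 28-day follow-up". By the synopsis and section 4.5, study treatment lasts up to 5 days and ends earlier on events such as ICU discharge or death.

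Other sections bear on the point without stating a prohibition:

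- Section 4.1 gives the assignment: "Patients will be allocated in a 1:1 ratio to either the treatment group, receiving Xuebijing Injection, or to control group, receiving placebo". Section 4.5 gives the length of the control course: "For control group -5 days of placebo has been administered".
- Section 4.4 says "Investigators and evaluators do not know the subject group information during the study and evaluation" and, under Figure 1, that "only drug managers and study nurses who prepared the study drugs are aware of the allocation information of subjects".
- Section 4.6 leaves patient management wholly to the ICU team. It asks for detailed recording of anti-infectives, hormones and anticoagulants, and does not name Xuebijing.
- Section 7.4 says "A protocol deviation may be an omission, addition or change in any procedure described in the protocol".
- Section 9.2 states that the investigational drugs are approved in China.
- The exclusion criteria in section 3.4 do not mention Xuebijing use.

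**The concern.** The list names Xuebijing in the window where it matters less and omits it in the window where the two arms are meant to differ. Sites consult 4.7 to learn what they may not give. Read item against item, it does not tell them that a commercial supply of this approved product is off limits while the blinded infusion is running.

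Two things are at stake. First, section 8.2 analyses by intention-to-treat, so a placebo patient who receives open-label Xuebijing still counts as placebo. If the drug works, the 28-day mortality difference shrinks toward zero. Second, an investigator who does not know the allocation and adds open-label drug to a patient already on active treatment could double the dose.

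**Working it through.** **Text check.** The treatment of each product by window under 4.7:

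| Window | Ulinastatin | Non-study Xuebijing |
|---|---|---|
| Treatment period (up to 5 days) | barred | not mentioned |
| End of treatment to day 28 | barred | barred |

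Sections 4.1 and 4.5 say which study infusion each arm receives, not what may be added to it. Section 7.4 allows such an addition to be called a deviation afterwards, but gives no instruction beforehand. The table's empty cell is therefore filled only by implication.

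**The plan's sample size.** Inputs from section 8.1: placebo mortality 24.3%, absolute reduction 6% (so 18.3% on Xuebijing), two-sided 0.05, 80% power, 15% dropout, N = 1800.

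With p̄ = (0.243 + 0.183)/2 = 0.213,

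n = [1.96·√(2·p̄(1−p̄)) + 0.842·√(0.243·0.757 + 0.183·0.817)]² / 0.06² = 730 per arm.

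- Without continuity correction: 2 × 730 / 0.85 = 1718.
- With continuity correction: n = 763 per arm, and 2 × 763 / 0.85 = 1796, which matches 1800.

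After 15% dropout, 1800 leaves 1800 × 0.85 / 2 = 765 per arm.

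**Illustration of dilution.** The documents give no rate of open-label use, so both inputs here are assumptions: a share c of placebo patients receives Xuebijing, and each gains a fraction f of the planned effect. The active-arm risk stays at 0.183.

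Placebo risk: p₁ = 0.243 − 0.06·c·f. Difference: Δ = p₁ − 0.183.

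Power = Φ[(Δ − 1.96·s₀)/s₁], where s₀ = √(2p̄(1−p̄)/n), s₁ = √((p₁(1−p₁) + 0.183·0.817)/n), and p̄ is recomputed from p₁. With continuity correction, Δ is reduced by 1/n.

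Worked case, n = 765, c = 0: s₀ = 0.02093, s₁ = 0.02088, (0.060 − 1.96 × 0.02093)/0.02088 = 0.909, power 81.8%.

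Full effect in exposed patients (f = 1):

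| c | Difference | 765/arm | 900/arm | 765/arm, corrected | 900/arm, corrected |
|---|---|---|---|---|---|
| 0 | 6.0 points | 81.8% | 87.5% | 80.1% | 86.3% |
| 5% | 5.7 points | 78.0% | 84.2% | 76.1% | 82.8% |
| 10% | 5.4 points | 73.7% | 80.4% | 71.6% | 78.7% |

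Half effect (f = 0.5), without correction: 80.0% at c = 5% and 78.0% at c = 10% with 765 per arm; 85.9% and 84.2% with 900 per arm. Only the product c·f matters, so half effect at 10% equals full effect at 5%.

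**The case against.** The strongest reply is that the protocol, read as a whole, has an obvious meaning: assigned product only during treatment, no Xuebijing afterwards. Item 1 could not name Xuebijing without a qualifier, and few sites would conclude that a placebo-controlled trial allows the test drug in its placebo arm for 5 days and bans it only later. The assigned regimens together with 7.4 support treating such use as a deviation. Blinding deters it too, because with 1:1 allocation a clinician adding the drug has an even chance of doubling an active patient's dose. The ICU-autonomy clause in 4.6 cannot be taken literally either, since it would then override the ulinastatin ban as well.

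The magnitude is also open to challenge. The crossover shares are assumed, full effect is an upper-end choice, and with all 900 per arm analysed power is still about 80% at 10% crossover. If Xuebijing is beneficial, the bias runs toward no difference and could not create a false claim of benefit.

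All of this stands as far as likelihood and size go. It explains the omission and makes frequent use less likely, but it does not supply the missing bar. The protocol already thought Xuebijing worth naming after treatment, and the reason for doing so is stronger during treatment.

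**Conclusion.** The concern holds. As written, section 4.7 does not expressly prohibit non-study Xuebijing in the treatment window, and no other section does. This is most likely a drafting gap, and nothing in the documents shows that contamination occurred or was expected.

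Its possible cost is modest and rests entirely on the assumed crossover. At 765 per arm, 5% to 10% full-effect crossover would cost about 4 to 8 points of power, with or without continuity correction. At half effect the loss, without correction, is about 2 to 4 points. On the basis that reproduces the planned 1800 (continuity-corrected, 15% dropout), power starts at 80%, so there is no reserve to absorb such a loss. If all 900 per arm are analysed, there is some. The point deserves correction as an inexpensive safeguard for the primary comparison and against double dosing.

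**What to change.** Replace item 1 of section 4.7 with wording such as: *From randomization to the end of the treatment period, ulinastatin and any Xuebijing injection other than the blinded study drug are prohibited in both arms.* Leave item 2 as it is.

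Record any non-study Xuebijing (dates and amount) up to day 28, if the CRF does not already do so. Section 7.1 mentions therapeutic interventions only in general terms, and the CRF is not shown.

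The cost is a short amendment, which under section 6.2 needs ethics re-review and re-approval, at up to 45 centres, and at most one added CRF item. It could be combined with another amendment if one is due. The sample size and the analysis do not change.
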